## Abstract

**Background:**

Frail older adults have reduced functional and physiological reserves, rendering them more vulnerable to the effects of hospitalization, which frequently results in failure to recover from the pre-hospitalization functional loss, new disability or even continued functional decline. Alternative care models with an emphasis on multidisciplinary and continuing care units are currently being developed. Their main objective, other than the recovery of the condition that caused admission, is the prevention of functional decline. Many studies on functional decline have discussed the available evidence regarding the effectiveness of acute geriatric units. Despite the theoretical support for the idea that mobility improvement in the hospitalized patient carries multiple benefits, this idea has not been fully translated into clinical practice.

**Methods/design:**

This study is a randomized clinical trial conducted in the Department of Geriatrics of a tertiary public hospital with 35 beds allocated. Hospitalized patients who meet the inclusion criteria will be randomly assigned to the intervention or control group. The intervention will consist of a multicomponent exercise training programme, which will be composed of supervised progressive resistance exercise training, balance-training, and walking for 5–7 consecutive days. During the training period, patients will be trained in 20 min sessions twice a day (morning and evening).

**Discussion:**

Functional and cognitive impairment after and during acute hospitalization in older adults is a major determinant of the later need for health resources. If our hypothesis is correct and shows that a multicomponent, individualized and progressive exercise programme provides effective therapy for improving the functional capacity of acute elderly patients hospitalized for medical pathology versus conventional care, a change of the current system of hospitalization of elderly patients with medical conditions may be justified.

**Trial registration:**

ClinicalTrials.gov Identifier: NCT02300896 (Date of registration 19 November 2014)

## Background

Frail older adults have reduced functional and physiological reserves, rendering them more vulnerable to the effects of hospitalization, which frequently results in failure to recover from the pre-hospitalization functional loss [1], new disability [2], or even continued functional decline [3]. Furthermore, consequences arise at multiple levels including cognitive impairment, longer hospital stays and institutionalization, poor mood, delirium, deconditioning, aspirations, pressure ulcers, falls, decreased caloric intake, social isolation, poor quality of life, increased use of health-related resources, disability and death [3–16].

Traditional risk factors for functional decline secondary to hospitalization are usually associated with comorbidities, malnutrition, depression, age, severity of illness and cognitive status [17–19]. However, the current model of care for hospitalized older adults plays an important role as a risk factor for in-hospital functional deterioration and has only recently begun to be evaluated [4, 20]. In-hospital mobility seems to be directly related to post-hospitalization functional outcomes [4, 20] and is one of the strongest predictors of functional decline. Hospitalized elderly patients are often bedridden; some studies show that more than 83 % of these patients are bedridden versus 4 % who are permitted to stand or walk [21, 22]. In older adults hospitalized for nondisabling conditions, in-hospital risk factors such as low mobility account for immediate and 1-month post-hospitalization functional declines [23]. Furthermore, illnesses and injuries that lead to hospitalization increase the likelihood of transitioning from non-frail to pre-frail, frail, or greater frailty states. Moreover, increasing evidence has shown that many older individuals have the capacity to recover from frailty and pre-frailty, although the likelihood of attaining a less frail state is lower. This probability can be reduced by approximately 50 % for each intervening hospitalization [24]. The figures regarding functional decline during hospital admission are heterogeneous and vary from 38-80 % depending on the study [10, 20, 25–27]. In a study conducted in our department [28], secondary functional impairment on admission was noted in 80 % of the patients susceptible to such impairment, persisting at discharge in 30 % of the patients.

Muscle strength and aerobic capacity decrease rapidly as a result of immobilization. After only ten days of rest, a healthy elderly person can lose 12–14 % of their VO_2max_ and muscle strength in the lower extremities [29]. In addition, skeletal muscle power decreases more rapidly than muscle strength with advancing age [30] and is also strongly associated with functional outcomes and functional capacity in elderly individuals at risk of disability [31, 32]. At the muscular level, reduced muscle use is associated with myofibrillar protein loss, muscle atrophy, and impaired control of the recruitment of motoneurons; at the clinical level, reduced muscle use is associated with decreased coordination, muscle strength, power output, aerobic capacity, balance, and exercise tolerance [5]. The consequences usually extend over time, and may produce long-term effects [30].

Alternative care models for an emphasis on multidisciplinary and continuing care units are currently being developed. Their main objective, other than the recovery of the condition that caused admission [32], is the prevention of functional decline. Many studies on functional decline have discussed the available evidence regarding the effectiveness of acute geriatric units [33, 34]. Despite the theoretical support for the idea that mobility improvement in the hospitalized patient carries multiple benefits, this idea has not been fully translated into clinical practice, and some studies have found paradoxical results [35]. The new models include exercise as an essential part of conventional treatment, at least when the patients are discharged to their homes [36]. Simple and basic procedures such as increasing the walking duration by 12 min or daily slow walking can reduce the average hospital stay [37]. In all of these circumstances, a comprehensive geriatric assessment of this type of patient should also consider the close link between the functional and cognitive situations, in addition to the previous theoretical concepts [38].

Exercise and early rehabilitation programmes are among the mechanisms by which functional and cognitive decline is prevented during hospitalization. Although risk factors associated with hospitalization and functional decline after discharge have been intensively studied, few randomized clinical trials have examined the potential benefits of conducting standard exercise programmes for hospitalized acute elderly medical patients. Nevertheless, the theoretical framework allows us to grasp the scope of possible improvement that exists for this population sector when such interventions are applied properly and selectively. The benefits of exercise have been clinically, biologically and even economically confirmed [39, 40], making exercise part of the therapeutic arsenal at our disposal. Multicomponent programs, and especially resistance exercise that includes muscle power training, are currently the most relevant interventions to slow down disability and other adverse outcomes, but these programmes have not been tested in acute geriatric patients. Moreover, to be effective, exercise has to be prescribed with a progressive individualized plan, similar to other medical treatments [31]. Some prospective studies have previously shown that hospitalization of older adults in a suitable environment can reduce disability and enhance the recovery of compromised activities during and after the acute event, which is contrary to some theories that highlight only the negative aspects or removal from the living environment [41].

The Cochrane reviews regarding exercise for acutely hospitalized elderly medical patients included only seven randomized controlled trials and two controlled clinical trials out of 3138 potentially relevant articles; the effect of exercise on measures of functional outcome was uncertain, and no effects of intervention on adverse events were found. A small reduction in the stay and total hospital costs (silver-level evidence) was found [42]. However, very few studies have explored the feasibility of conducting exercise programmes for hospitalized acute elderly patients [43]. Furthermore, evidence is lacking to determine which types of hospitalized elderly patients would benefit more from each programme and whether each programme is viable.

## Study design and setting

This study is a randomized clinical trial conducted in the Department of Geriatrics of a tertiary public hospital with 35 beds allocated. Hospitalized patients who meet the inclusion criteria will be randomly assigned to the intervention or control group. Patient recruitment will begin within the first 48 h of admission to the ward, and these patients will be identified through a list of patients admitted to the hospital and assigned to the Department of Geriatrics. The study flow diagram is shown in Fig. 1. After signing an informed consent form, the subjects will be randomly assigned (as explained below) to either the intervention or control group. The researcher who decides whether the patient is assigned to the intervention or control group will not be the attending physician. Patients or their relatives (if the patient has cognitive impairment) will be informed of the random inclusion in one group, but will not be informed as to which they belong. The data for both the intervention group and the control group will be obtained at four different times: the initial visit during the acute hospitalization, at discharge, and at one and three months after discharge from the outpatient clinic. Time of measurement of the different variables is shown in Table 1. The protocol employs relevant standard protocol items for clinical trials according to the SPIRIT 2013 statement [44] and follows the CONSORT statement [45] for transparent reporting. The trial is registered at ClinicalTrials.gov, identifier NCT02300896.

**Fig. 1 Fig1:**
[figure not shown]
Flow diagram of the study protocol

**Table 1 Tab1:** Time of measurement of the different variables on the participants of the study

Measurement	T1 Baseline	T2 After training or control period	T3 1-month	T4 3-months
Categorical scale of pain	X	X	X	X
Barthel Index	X	X	X	X
Geriatric depression Scale of Yasavage	X	X	X	X
Mini-Mental State Examination (MMSE)	X	X	X	X
Short Physical Performance Battery (SPPB)	X	X	X	X
Gait Velocity Test (GVT)	X	X	X	X
Dual-task (verbal and counting GVT)	X	X	X	X
Maximal isometric force of handgrip, knee extension and hip flexion	X	X	X	X
1RM (Leg press, Chest press and Knee extension)	X	X	X	X
Muscle power at 50 % 1RM in Leg press	X	X	X	X
Confusion Assessment Method (CAM)	X	X	X	X
Quality of Life (EQ-5D)	X	X	X	X
Geriatrics syndromes	X	X	X	X
Isaacs set test	X	X	X	X
Trail Making Test (TMT)	X	X	X	X
Laboratory parameters	X			
Diseases considered grouped by ACG of Salisbury and CIE-10 codes	X			
Cumulative Illness Rating Scale for Geriatrics (CIRS-G)	X			
Zarit Scale	X			
Falls	X	X	X	X
Mini Nutritional Assessment (MNA)	X			

Adverse events, including muscle pain, fatigue, and general aches and pains will be recorded by the training and testing staff and by self-report during the study period. We will also record the number of falls during the study and for one year prior to admission.

This study has been approved by the Navarra Clinical Research Ethics Committee (Pyto 23/2014).

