### Randomization and blinding

The study participants will be randomized (www.randomizer.org) into an intervention group and a control group. Participants will be explicitly informed and reminded not to discuss their randomization assignment with the assessment staff. The assessment staff will be blinded to the participant randomization assignment, as well as to the main study design and to what changes we expect to occur in the study outcomes in either group.

It will not be possible to conceal the group assignment from the staff involved in the training of the intervention group.

Patients or their families (if the patient has cognitive impairment) will be informed of the random inclusion in one group, but will not be informed as to which group they belong.

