	Chet press	1RM + 1×10 (30 % 1RM)	2×10 (30 % 1RM)	3×10 (40 % 1RM)	3×10 (50 % 1RM)	3×8 (60 % 1RM)	3×8 (60 % 1RM)	3×8 (60 % 1RM)
	Leg extension	1RM + 1×10 (30 % 1RM)	2×10 (30 % 1RM)	3×10 (40 % 1RM)	3×10 (50 % 1RM)	3×8 (60 % 1RM)	3×8 (60 % 1RM)	3×8 (60 % 1RM)
Afternoon	Leg extension (0,5 – 1,0 Kg)		2×10	2×10	2×10	2×10	2×10	2×10
	Leg flexion (0,5 – 1,0 Kg)		2×10	2×10	2×10	2×10	2×10	2×10
	Hip abduction (0,5 – 1,0 Kg)		2×10	2×10	2×10	2×10	2×10	2×10
	Hand grip ball		2×10	2×10	2×10	2×10	2×10	2×10

*In case that the patient is still hospitalized

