### Outcome measures

#### Primary outcome

The primary outcome measure is the change in functional and cognitive status during the study period. The functional capacity of patients will be evaluated by the Short Physical Performance Battery (SPPB) [47], which evaluates, balance, gait ability, and leg strength using a single tool. The total score will range from 0 (worst) to 12 points (best). The SSPB test has been shown to be a valid instrument for screening frailty and predicting disability, institutionalization, and mortality. A total score of less than 10 indicates frailty and a high risk of disability and falls. One-point change in the score has clinical relevance [48, 49]. Loss of handgrip of the dominant hand is a useful tool for the measurement of functional capacity. It is a strong predictor of disability, morbidity, and mortality as well as one of the components of Fried’s frail phenotype. Furthermore, the functional status of patients will also be assessed before measurements with the Barthel Index, an international and validated tool of disability. The scores range from 0 (severe functional dependence) to 100 (functional independence) [50]. Gait ability will be assessed using the 6-metre gait velocity test (GVT). Starting and ending limits will be marked on the floor with tapelines for a total distance of 8 m. Participants will be instructed to walk in their self-selected usual pace for two attempts. The results of both trials will be averaged to obtain a single value. The first and last metre, considered the warm-up and the deceleration phases, respectively, will not be included in the calculations of the gait assessment. Dual task conditions (gait evaluation during the simultaneous performance of a cognitive motor action) have recently been recognized as a sensitive assessment method for interactions between cognition, gait, falls and frailty. Changes of gait parameters (i.e., gait velocity and gait variability) while performing a dual task test (dual task cost) could be early predictors of falls risk (50) and useful tools for functional evaluations in frail elderly patients. Exercise can modify dual task cost and consequently fall risk and functional capacity (31). The dual-task paradigm [51] will be used in the 6-m habitual gait velocity test (GVT). Two trials will be performed to assess the gait velocity while performing a verbal or counting task (verbal GVT and counting GVT, respectively). During the verbal dual-task condition (verbal GVT), we will measure the gait velocity while participants are naming animals aloud. During the arithmetic dual-task condition (counting GVT), we will assess the gait velocity while participants are counting backward aloud from 100 by ones. The cognitive score will be measured by counting the number of animals named (dual-task with verbal performance) or determining how many numbers were counted backward (dual-task with arithmetic performance). Isometric upper (right hand grip) and lower limb (right knee extensors and hip flexors) muscle strength will be measured using a manual dynamometer. Maximal dynamic strength will be assessed using the 1RM test in the bilateral leg press, knee extension and bench press exercises using exercise machines (Exercycle, S.L., BH Group, Vitoria, Spain). In the first assessment, the subjects will warm up with specific movements for the exercise test. Each subject's maximal load will be determined in no more than five attempts, with a 3-min recovery period between attempts. After determination of the 1RM values, the subjects will perform ten repetitions at maximal velocity at intensities of 50 % of 1RM to determine the maximum power (w) and the loss of power during the ten repetitions in the leg press machine. The power will be recorded by connecting a velocity transducer to the weight plates (T-Force System, Ergotech, Murcia, Spain). During all neuromuscular performance tests, a strong verbal encouragement will be given to each subject to motivate them to perform each test action as optimally and rapidly as possible. Qualified fitness specialists will individually monitor and carefully supervise all training sessions and provide instruction and encouragement during all sessions. Distribution of the training sessions throughout the day should minimize cumulative fatigue and help to maintain adherence. Adherence to the exercise intervention programme will be documented in a daily register of sessions. Changes in cognitive-affective status after the intervention will be measured using the Mini Mental State Examination, Yesavage GDS and Trail Making Test (Table 3).

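### Testing staff who are to stay blind also share in recording muscle pain and fatigue, which opens an avoidable route to unblinding for effort-dependent primary tests

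*Protocol article*

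**What the plan says.** **Who records symptoms.** The text after Table 1 (Study design and setting) assigns the task to two staff groups and to the patient: "Adverse events, including muscle pain, fatigue, and general aches and pains will be recorded by the training and testing staff and by self-report".

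**Who must be blind.** The section on randomization and blinding states: "The assessment staff will be blinded to the participant randomization assignment, as well as to the main study design". It adds that these staff should not know which changes are expected in either group. For trainers the position is the reverse: "It will not be possible to conceal the group assignment from the staff involved in the training of the intervention group".

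**What protects the blind.** The stated measure against disclosure is an instruction to patients: "Participants will be explicitly informed and reminded not to discuss their randomization assignment with the assessment staff". The same section also says that patients, or relatives where the patient is cognitively impaired, are not told which group they are in.

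**What the assessors measure.** Under the primary outcome, "The primary outcome measure is the change in functional and cognitive status during the study period". The SPPB, gait and dual-task tests, grip and leg strength, machine-based strength and power, and cognitive and mood scales are described there. In the neuromuscular tests, "a strong verbal encouragement will be given to each subject to motivate them to perform each test action as optimally and rapidly as possible". Table 1 repeats these measurements at baseline, after the training or control period, and at one and three months.

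**The concern.** The intervention is supervised exercise twice a day for five to seven days, so patients cannot in practice be masked to what they receive. Blind assessment is therefore the main protection of the primary comparison. Most of these tests depend on how hard the patient tries, and a tester who is told to urge patients on can do so more or less strongly.

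Recording muscle pain or fatigue usually means hearing the patient's own account. In this trial that account may include the training sessions. A rule that has the assessors collect it gives them a reason to hear about the one thing they are supposed not to know. If the same staff return for the one-month and three-month visits, a disclosure after the training period could carry over to those visits.

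**Working it through.** No arithmetic applies: the document gives neither a disclosure rate nor an effect of unblinding on scores. The check sets the passages side by side.

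1. **Same people or not?** The text after Table 1 speaks of training and testing staff; the blinding section speaks of assessment staff and of staff who train. The article describes no third group that tests patients, so the natural reading equates testing staff with assessment staff. This is an inference, because the article never says so.

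2. **Do the two rules conflict?** One keeps assessors blind to assignment and to the main design. The other has them share a symptom record with trainers who know the arm. Nothing in the article separates the two groups' recording. The rules can coexist only if no patient's account points to exercise sessions.

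3. **Does the safeguard close the gap?** Only in part, for three reasons.
   - Answering a question about sore muscles is not obviously a discussion of assignment.
   - A patient who has not been told the group may not know which remark reveals it.
   - The article provides for patients with cognitive impairment and names only severe dementia (GDS 7) as an exclusion on that ground, so some patients may find the instruction hard to keep. The requirement that patients be capable of consent tempers this reason without removing it.

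4. **Are the exposed measures important?** Yes. They are described under the primary outcome, and encouragement gives a tester who knows the arm a way to affect performance.

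5. **Are the training and testing roles clear for the machine tests?** No. Under the primary outcome, "Maximal dynamic strength will be assessed using the 1RM test in the bilateral leg press, knee extension and bench press exercises using exercise machines". Table 2 also places a 1RM for leg press, chest press and leg extension in the Day 1 training session. The article does not say whether that is the baseline test or a separate one, or whether blinded assessors or trainers run it.

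**The case against.** The strongest reply is that the named symptoms are general ones. They are not tied to training or to one arm, and they are common in acutely ill inpatients aged 75 or older. Controls also undergo maximal strength testing and receive rehabilitation when needed. The sentence can be read as ordinary safety recording, in which each group notes what arises in its own sessions; no symptom interview is described. Patients are told and reminded to keep their assignment to themselves, and assessors are also kept unaware of the expected changes, which makes a directional bias less likely even if the arm leaks.

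Much of this stands. It shows that the symptoms hint at the arm and do not reveal it. It does not remove the conflict, because the article neither limits testing staff to events arising during testing nor says when they make the record.

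Several stronger readings are tempting, and the document does not support them:

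- **That the visits have no fixed order, or that complaints are heard before the primary tests.** The Barthel Index is set before the measurements and the power test after the 1RM. Both Table 1 and the outcome text list SPPB and gait ahead of 1RM. Table 1 lists the pain scale first, but it is not stated to be a visit sequence. A full sequence is detail that an article may leave to the full protocol.
- **That familiarity with the machines gives the arm away.** Training is described on Matrix machines and strength testing on Exercycle machines. Both arms are tested at every visit, so controls have also met the tests at baseline. The afternoon leg extension in Table 2 uses light weights and is not the machine exercise. Familiarity is at most an indirect clue.
- **That the bias can be stated in SPPB points.** The article calls a one-point change clinically relevant. Any bias figure to set against it would be a product of two assumptions, the share of patients who disclose and the resulting shift in rating, and neither has a source in the document.

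**Conclusion.** The point holds as a conflict between two stated rules that creates an avoidable route to unblinding. It does not hold as a claim that assessors are unblinded, that this happens before particular tests, or that the primary result is biased by a known amount. The size cannot be determined from the document.

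The conclusion rests on two assumptions: that the testing staff are the blinded assessment staff, and that recording symptoms involves hearing the patient's explanation. Carry-over to later visits needs a third, that some of the same assessors return. If the full protocol separates the roles, or confines assessors to recording after their tests, the point falls away and the article needs only a clarifying sentence.

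It is worth making because the exposed tests belong to the primary outcome, patients cannot be masked, and the remedy is nearly free. It is a cheap improvement and not a fatal flaw.

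**What to change.** - Reconcile the text after Table 1 with the blinding section. Have existing staff who do not assess outcomes collect adverse-event and symptom reports, with the same questions in both arms.
- Where testing staff must record an event themselves, for example one that arises during testing, have them do so only after that visit's outcome tests are finished. This concerns the timing of the study record, not how an event is handled.
- State whether the blinded assessors run the 1RM tests, and how those tests relate to the 1RM that Table 2 places in the Day 1 training session.
- Optional: a fixed encouragement script, and a form on which assessors record their guess of the arm.

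The cost is a short recording duty moved to other staff, with no new measurement of the patient. The downside is that those staff may know the arm, especially on a 35-bed unit where training is visible, so symptom reports would be collected unblinded while the efficacy tests stay protected. Common questions in both arms limit that loss. Recruitment was still open when the article was written, so the change could still serve the remaining participants and visits.

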The supervised multicomponent exercise training programme will be comprised of upper and lower body strengthening exercises, tailored to the individual’s functional capacity, using weight machines and aiming for 2–3 sets of 8–10 repetitions at an intensity of 30–60 % of 1RM (Matrix, Johnson Health Tech, Ibérica, S.L. Torrejón de Ardoz, Madrid, Spain) combined with balance and gait retraining exercises that progressed in difficulty and functional exercises, such as rises from a chair. The second part of the session will consist of functional exercises such as knee extension and flexion, hip abduction, balance movements, and daily walking in the hospital. A minimum of 2 days elapsed between consecutive training sessions. The resistance exercises focused on the major upper and lower limb muscles. Each resistance training session will include 2 exercises for the leg extensor muscles (bilateral leg extension and bilateral knee extension muscles) and 1 exercise for upper limbs (seated bench press). During the progressive resistance training, instruction will be provided to the participants to perform the exercises at a high velocity of motion. However, care will be taken to ensure that exercises were executed with correct form. In each session, subjects will perform a specific warm-up with one set of very light loads for the upper and lower body. Balance and gait retraining exercises that progressed in difficulty will be also implemented: semi-tandem foot standing, line walking, stepping practice, walking with small obstacles, proprioceptive exercises on unstable surfaces (foam pads sequence), and altering the base of support and weight transfer from one leg to the other. One experienced physical trainer will carefully supervise all training sessions. The training sessions will last for approximately 40 min. The approximate duration of each part of the training will be: 5 min of warm-up, 10 min balance and gait retraining, 15 min of resistance training, and five minutes of stretching (cool-down). The training protocol is shown in Table 2. Participants and their family members will be carefully familiarized with the training procedures in advance.

**Table 2 Tab2:** Intervention group exercises

	Exercise	Day 1	Day 2	Day 3	Day 4	Day 5	Day 6*	Day 7*
Morning	Rises from a chair	1×5	1×10	2×10	3×10	3×8	3×8	3×8
	Leg press	1RM + 1×10 (30 % 1RM)	2×10 (30 % 1RM)	3×10 (40 % 1RM)	3×10 (50 % 1RM)	3×8 (60 % 1RM)	3×8 (60 % 1RM)	3×8 (60 % 1RM)

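### One of three adverse-event recording channels, the unblinded trainers, in effect serves the exercise arm only, and the statement that patients will not be told their group cannot hold

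*Protocol article*

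**What the plan says.** **Adverse events.** The note after Table 1 (Study design and setting) covers "Adverse events, including muscle pain, fatigue, and general aches and pains" and says that these "will be recorded by the training and testing staff and by self-report during the study period". That makes three channels: trainers, testers and the patients themselves.

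**Who is blinded.** Randomization and blinding says of the trainers: "It will not be possible to conceal the group assignment from the staff involved in the training of the intervention group". Of the testers it says: "The assessment staff will be blinded to the participant randomization assignment, as well as to the main study design".

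**What participants know.** The same section says that patients or their families "will not be informed as to which group they belong", and Study design and setting makes the same statement. Yet Randomization and blinding also says: "Participants will be explicitly informed and reminded not to discuss their randomization assignment with the assessment staff". Intervention group (training) adds: "Participants and their family members will be carefully familiarized with the training procedures in advance".

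**Scheduled assessments.** Study design and setting says: "The data for both the intervention group and the control group will be obtained at four different times". Table 1 lists the pain scale, falls, EQ-5D and the Yesavage scale at T1 to T4, with no difference by arm.

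**The concern.** Muscle pain, fatigue and aches are subjective. Whether they are recorded depends largely on whether someone asks or is present when the patient complains. If one arm has an extra observer on most days of the stay and the other does not, recorded rates can differ when true rates do not. The error would run against exercise and could make a harmless programme look less well tolerated.

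The second issue is separate. A reader who takes the participant-information sentences at face value may give the self-reported outcomes more protection from expectation than they have. The Yesavage scale is named under the primary outcome and EQ-5D is a secondary outcome, so this touches listed endpoints.

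**Working it through.** The article gives no figure on this point to reproduce. The check is a comparison of passages, followed by an illustration on assumed values.

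**1. Which channels exist in which arm**

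| Channel | Intervention | Control | Blinded | Source |
|---|---|---|---|---|
| Training staff | Yes | None described | No | Randomization and blinding; Usual care group; Intervention group |
| Testing staff | Yes | Yes | Yes | Study design and setting; Randomization and blinding |
| Self-report | Yes | Yes | No (step 3) | Note after Table 1 |

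No sentence says that trainers never meet controls. It follows from their being tied to the training of the intervention group, from one trainer supervising every session, and from controls receiving normal hospital care with rehabilitation when needed. I also take the testing staff and the assessment staff to be the same people.

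Trainer contacts by Table 2: morning exercises on every day, afternoon exercises from day 2.
- Five days: 5 + 4 = 9 sessions.
- Seven days: 7 + 6 = 13 sessions.
- Controls: none.

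The sentence in the same section requiring at least two days between sessions does not fit this table and must be reconciled with it. Either way, the contact is in one arm only.

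**2. How large the distortion could be**

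Assume an equal true event risk *p* in both arms. The common channels detect a share *s* of events. Trainers detect a share *t*, independently and in the intervention arm only.
- Recorded, control: *p s*
- Recorded, intervention: *p* [1 − (1 − *s*)(1 − *t*)]
- Ratio: [1 − (1 − *s*)(1 − *t*)] / *s* = 1 + *t*(1 − *s*)/*s*, which does not depend on *p*

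With *p* = 0.20, the planned 185 per arm and a two-sided 0.05 test:

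| *s* | *t* | Control | Intervention | Ratio | Chance of a significant false excess under exercise |
|---|---|---|---|---|---|
| 0.9 | 0.25 | 18.0% | 18.5% | 1.03 | 3.3% |
| 0.7 | 0.5 | 14.0% | 17.0% | 1.21 | 12.2% |
| 0.5 | 0.8 | 10.0% | 18.0% | 1.80 | 60.2% |

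Middle row: 0.20 × 0.7 = 0.14; 0.20 × [1 − 0.3 × 0.5] = 0.20 × 0.85 = 0.17; 0.17/0.14 = 1.21.

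Over *p* from 0.10 to 0.30, *s* from 0.5 to 0.9 and *t* from 0.25 to 0.8, the ratio runs from 1.03 to 1.80. The chance of a false excess runs from about 3% to 81%, against a nominal 2.5% in that direction. The model treats all events as open to trainer detection. Trainers are present for only 5 to 7 inpatient days, while follow-up runs to three months after discharge. If only part of the counted events fall in those days, the excess of the ratio over 1 shrinks in proportion.

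**3. Participant knowledge**

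The statements cannot all be true in practice. Patients are said not to be told their group, yet are reminded not to discuss their assignment, which presumes that they know it. Patients and families are introduced to the training beforehand. The eligibility criteria exclude anyone unwilling to be randomized to either group, so participants know that two arms exist. Attending supervised sessions on weight machines, or not attending them, then reveals the arm.

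**The case against.** **Two of the three channels are symmetric.** This stands. Testers are blinded and see both arms at the same four times, and self-report is open to everyone. A reader might infer that trainers alone record adverse events, or that every safety comparison is distorted. The text does not support that: pain and falls are scheduled identically in both arms.

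**No between-arm adverse-event test is specified, and adverse events are not a listed primary or secondary outcome.** This is correct, and how events are tabulated may properly be left to a fuller document. The point is therefore conditional: it concerns any comparison that pools the channels as described. The asymmetry itself is stated in the article, not an omission.

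**EQ-5D, Yesavage and pain share schedule and assessors.** Correct. A reader might call these differentially ascertained too. They are not; their exposure is response bias from knowing the arm.

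**No unblinding route is described.** Correct. A reader might infer that trainers' records reach the testers, but no passage says so. Both arms also undergo strength and power testing, so a complaint of muscle pain does not by itself reveal the arm.

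**The article applies the word blinded only to assessment staff.** Also correct. It does not claim a double-blind design. What remains is a sentence, given twice, that promises something the design cannot deliver and that conflicts with its own section.

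**The detection rates are invented.** They are assumptions, and the range starts close to no bias. The bias also runs against the intervention, so it would not make exercise look safer than it is.

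**Conclusion.** The point holds in a limited form.

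First, one of the three adverse-event channels is unblinded and, by strong inference, confined to the intervention arm. Pooling all channels would tend to inflate recorded events under exercise. The direction is clear but the size is not: the ratio is about 1.03 if the common channels already catch 90% of events and trainers a quarter, and up to 1.80 if the common channels miss half and trainers catch 80%. These rates are assumed, and the model takes detection to be independent across channels and all events to fall within reach of the trainers.

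Second, the statements that participants will not be told their group contradict other text and are not achievable, so self-reported measures come from people who know their arm. No number can be put on the resulting response bias from these documents.

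Neither point impugns the blinding of the assessors or the identically scheduled recording of falls and pain.

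**What to change.** 1. Base any between-arm adverse-event comparison on the channels common to both arms: the same questions, asked in the same way by the blinded testers at T2, T3 and T4.
2. Report trainer-recorded events separately, as a description of the intervention arm. As a precaution, keep that log from the testers.
3. Remove or reconcile the participant-information sentences in Study design and setting and in Randomization and blinding. Describe the trial as assessor-blinded only.
4. Label EQ-5D, the Yesavage scale, pain and self-reported adverse events as unblinded self-report.

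The visits already exist, so the cost is one short structured checklist and some rewording. The price is that events seen only by trainers between visits drop out of the between-arm comparison, and control events between visits rest on recall. The separate listing keeps the trainers' observations available for judging tolerability.
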